## 8.2. Secondary goals:

8.2.1. To evaluate the efficacy of the combination of ATO and antichagasic therapy to decrease:

- Inflammation, as measured by plasma levels of the cytokines, TNF- $\alpha$ , IFN- $\gamma$ , IL-10, IL-1B, IL-4, and IL-17A.
- Endothelial activation, as measured by plasma levels of sCAM: sE-selectin, sICAM-1, and sVCAM-1.
- Cardiac damage and function: measured by plasma levels of BNP, cTnT, 12-lead resting ECG (heart rate, QT segment duration, and electrical conduction changes determined by QRS segment duration and morphology), and 2D echocardiogram (ejection fraction).

8.2.2. To determine the safety and tolerability of the combination of ATO with antichagasic therapy, measured by the incidence of AEs (e.g., rhabdomyolysis) and treatment discontinuation.

8.2.3. To evaluate the treatment response to the combination of ATO with antichagasic therapy, as measured by quantitative PCR and serology, over a 10-month follow-up period.

8.2.4. To determine the degree of therapy adherence by measuring drug accountability throughout the study.

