|                                                             | A                                                                                                                                       | B1                                                                                                                                                                                                           | B2                                                                                                                                               | C                                                                                                        | D                                                                                                                           |
| Patients with findings compatible with acute Chagas disease | Patients at risk for developing CHF. They have positive serology, neither structural cardiopathy nor CHF symptoms. No digestive changes | Patients with structural cardiopathy, evidenced by electrocardiographic or echocardiographic changes, but with normal global ventricular function and neither current nor previous signs and symptoms of CHF | Patients with structural cardiopathy characterized by global ventricular dysfunction, and neither current nor previous signs and symptoms of CHF | Patients with ventricular dysfunction and current or previous symptoms of CHF (NYHA FC I, II, III or IV) | Patients with refractory symptoms of CHF at rest, despite optimized clinical treatment, requiring specialized interventions |

Arq Bras Cardiol 2011; 97(2 supl.3): 1-48

The **secondary outcome** is determined by the change in plasma levels of biomarkers versus changes in parasite load.

Additional measures of scientific value: (a) change in plasma levels of biomarkers of inflammation and endothelial activation; (b) incidence and severity of AEs; (c) change in parasite burden and serologic response over the follow-up period, measured by quantitative PCR (qPCR); (d) changes in biomarker levels at different follow-up time points and correlation with parasite burden and ATO regimen; and (e) incidence of treatment discontinuation due to severe AEs.

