| Pregnancy test                            | x         |          |           |    |                | x                | x                |     |
| Serology                                  | x         |          |           |    |                |                  |                  | x   |
| Laboratory                                | x         | x        | x         | x  | x              | x                | x                | x   |
| Quantitative PCR                          | x         |          |           |    | x d |                  |                  | x   |
| Biomarkers b                   |           | x        |           | x  | x              |                  |                  | x   |
| Focused Physical Examination c | x         | x        | x         | x  | x              | x                | x                | x   |
| Adverse Events                            |           |          | ←-----→   |    |                |                  |                  |     |
| Drug Accounting                           |           | x        | x         | x  | x              |                  |                  |     |

aLaboratory parameters will include: hemoglobin, total white blood cell count, differential white blood cell count, and platelet count. Laboratory biochemical parameters will include: CK, ALT, AST, GGT, alkaline phosphatase, total and direct bilirubin, a lipid profile: total cholesterol, c-HDL, and c-LDL, triglycerides, fasting blood glucose, and creatinine;

bBiomarkers: BNP, cTnT, IFN-γ, IL-1β, IL-4, IL-17A, e IL-10, sICAM-1, sVCAM-1, sE-selectin;

cPhysical examination focused only on the evaluation of adverse events.;

dPCR testing at these time points will be done with a single 10 ml sample;

eECGs will be performed at these visits only in case of previously identified abnormalities

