### **12.Data analysis and statistical methods:**

#### **12.1. Sample size:**

A sample size of 75 patients per group is sufficient to achieve a power of 90% at an overall significance level of 5% (2-sided), assuming that the proportion of patients who improve electrocardiographic and echocardiographic parameters, as well as the levels of the cardiac function markers BNP and cTnT in the EOT in the experimental treatment group is 0.40. The proportion in the placebo group is 0.20, with an odds ratio of 2.5. Considering an estimated dropout rate of 25%, 100 patients per group (300 patients in total) would be recruited (Fleiss et al., 2003). The study will be sufficiently powered to provide evidence of the superior efficacy of either statin dose plus antichagasic therapy relative to antichagasic treatment alone.

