### **12.4. Efficacy analysis:**

For analysis of the primary outcome, a one-sided Fisher's exact test of the proportion of patients with a significant decrease in biomarker levels in the ITT (primary analysis) and per protocol (secondary analysis) populations will be used. ANOVA test will be performed to analyze differences in variances between the different markers. An exact test will be performed for all secondary comparisons of proportions between ATO versus placebo, including parasitological response to treatment. Latent class and multivariate analyses will assess the association between parasitological response, biomarker changes, and ATO doses.

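### Section 12.4 tests the primary outcome on an unspecified biomarker decrease that does not match Sections 8.1, 9.1 and 12.1, and its wording leaves the 5% error rate unsecured

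*Protocol*

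**What the plan says.** **The test.** Section 12.4 analyses the primary outcome with a one-sided Fisher's exact test of "the proportion of patients with a significant decrease in biomarker levels in the ITT (primary analysis"), with the per-protocol population as a secondary analysis. No alpha is stated there. The same section continues: "An exact test will be performed for all secondary comparisons of proportions between ATO versus placebo, including parasitological response to treatment". The Summary repeats both statements.

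**The outcome.** Section 8.1 counts patients whose cardiomyopathy stage changes within 12 months. Section 9.1 uses change of phase at 12 months and brings in BNP and cTnT as additional findings. Section 12.1 assumes response rates of 0.40 and 0.20 for improvement in ECG and echocardiographic parameters together with BNP and cTnT, at end of treatment, and states the design "at an overall significance level of 5% (2-sided").

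**The panel.** Sections 9.6 and 9.7 list ten assayed markers: BNP, cTnT, IFN-γ and IL-1β, then "IL-4, IL-17A, e IL-10, sICAM-1, sVCAM-1, sE-selectin". They are drawn at baseline and on days 60, 120 and 360. Section 8.2.1 also lists TNF-α, and introduces the cytokines, adhesion molecules and cardiac markers with "To evaluate the efficacy of the combination of ATO and antichagasic therapy to decrease". Section 9.1 places cytokine and adhesion-molecule changes in a lower tier of additional measures, which includes "changes in biomarker levels at different follow-up time points and correlation with parasite burden and ATO regimen".

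**Multiplicity.** The only statement is in the Summary: if the two atorvastatin doses do not differ significantly they are collapsed, and no adjustment is then made.

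**The concern.** The primary test is the one place where the protocol must leave no choice. As written, an analyst could use one composite responder rule, BNP and cTnT only, or each of the ten markers in turn, and could choose the visit. These options have very different error rates, and the protocol does not say which applies.

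Direction is also unsettled. Section 12.4 counts a decrease as success, while Section 7.1.3.1 describes IL-4 and IL-10 as anti-inflammatory and links higher IL-17A to milder heart disease. Without a named marker or rule, a fall in one of these could be reported as benefit.

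If the test were run marker by marker, an inert drug could be reported as lowering inflammation, endothelial activation or cardiac damage on whichever marker happened to cross the threshold. A proof-of-concept decision could then rest on that result.

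**Working it through.** **1. Passages side by side.**

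| Section | What is assessed | When | Markers |
|---|---|---|---|
| 8.1 | change of cardiomyopathy stage | 12 months | none |
| 9.1 | change of phase | 12 months | BNP, cTnT, additionally |
| 12.1 | improved ECG, echo, BNP, cTnT | end of treatment | BNP, cTnT |
| 12.4, Summary | significant decrease in biomarker levels | not stated | not stated |

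Section 12.1 does not settle the visit. Atorvastatin or placebo starts after about 60 days of antichagasic treatment and a two-week gap, so at about day 74. Eight weeks (Section 9.5) then ends at 74 + 56 = day 130. Four months (Section 9.3) ends at about 74 + 120 = day 194. Biomarkers are drawn on days 60, 120 and 360, so neither date has a scheduled draw. The two durations must be reconciled.

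**2. The plan's own figure.** Inputs from Section 12.1: 0.40 against 0.20, 90% power, two-sided 5%.

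n = [1.960·√(2·0.30·0.70) + 1.282·√(0.40·0.60 + 0.20·0.80)]² / 0.20² = (1.270 + 0.811)² / 0.04 ≈ 108.2, so 109 per group.

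The stated 75 is not reproduced; at 75 per group the power is about 77%. That is a separate matter. Below, 75 and 100 per arm serve only as sample sizes.

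**3. One pre-defined responder test.** Exact size of the one-sided Fisher test at nominal 5%, with a true rate of 0.20 in both arms: sum the product of the two binomial probabilities over all tables whose hypergeometric upper tail is at most 0.05. The result is 3.3% at 75 per arm and 3.5% at 100 per arm.

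**4. Several markers, one visit, one comparison, independent.** The chance of at least one false positive is 1 − (1 − s)^k.
- k = 10, nominal s = 0.05: 1 − 0.95¹⁰ = 40.1%.
- k = 10, exact s = 0.033 (75 per arm): 1 − 0.967¹⁰ = 28.5%. With s = 0.035 (100 per arm): 30.0%.
- k = 2 (BNP and cTnT), exact s = 0.033: 1 − 0.967² = 6.5%. Nominal: 9.75%.

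**5. The same with correlated markers.** Simulated null trials: 20% responders per marker in every arm, exchangeable latent normal correlation of 0.2, 0.5 or 0.8, one-sided Fisher test for each marker.
- Ten markers, one-sided 5%: about 22–23% at correlation 0.5. The range is about 16–28% over correlations 0.8 to 0.2 and 75 or 100 per arm.
- Ten markers, one-sided 2.5% (the benefit half of a two-sided 5% test): about 9–13%.
- Ten markers, both doses pooled against placebo, one-sided 5%: about 22% at correlation 0.5.
- BNP and cTnT only, one-sided 5%: about 5–7%.

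Simulation error is under one percentage point: with 4,000 trials, √(0.23·0.77/4000) = 0.7 points.

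**6. Sensitivity.** The 0.20 in Section 12.1 is a placebo rate for improving the cardiac parameters and markers together, not a rate for each marker. At 5% responders per marker, the ten-marker figure at one-sided 5% falls to about 13–18%.

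**The case against.** The strongest reply is that Section 12.4 describes one test of one proportion. A per-patient responder rule fits that wording at least as well as ten separate tests, and would have a true size of about 3%. Sections 9.1 and 12.1 name only BNP and cTnT among the markers, which gives about 5–7%. Section 9.1 does rank the outcomes and places the cytokines and adhesion molecules among additional measures. Alpha allocation across secondary markers in a phase II trial can also sit in the SAP, which is not available here.

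Most of this stands. A reader might infer that all ten markers will be tested at three visits and for both doses, making a false positive more likely than not. The documents do not support that: no section says the markers are tested separately, and the day-60 draw appears only in the sampling schedule, not as an efficacy comparison. Testing both doses separately and unadjusted at one visit would raise the ten-marker figure to about 28–42%, and more visits would raise it further. But the protocol does not state that this will be done. The Summary's waiver of adjustment for collapsed doses suggests that some adjustment was in mind otherwise. Nor does the overall 5% in Section 12.1 amount to a promise of control across every secondary marker.

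The reply does not repair the primary test. The protocol writes that test itself, on a variable that differs from the outcome in Sections 8.1 and 9.1, one-sided against two-sided sizing, and supplies no responder rule.

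**Conclusion.** The point holds as a badly fixed primary test, not as a forecast that a false positive is likely. Section 12.4 and the Summary leave marker, visit and responder rule open and disagree with Sections 8.1, 9.1 and 12.1. The 5% level is therefore secured on one reading and not on another.

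At one-sided 5%, one visit and one comparison, the chance of a false positive is about 3% for a single responder test, about 5–7% for BNP and cTnT separately, and about 16–28% for the ten markers separately. At one-sided 2.5% the ten-marker figure is about 9–13%.

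These figures rest on an assumed 20% responder rate per marker and assumed latent correlations of 0.2 to 0.8. Neither is given for the individual markers in the protocol. The change should be made before the analysis is fixed.

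**What to change.** In Section 12.4 and the Summary:
- Make the only alpha-bearing primary test a single per-patient outcome, with its responder rule written out and reconciled with Sections 8.1, 9.1 and 12.1. Name one visit after atorvastatin or placebo has started, and state the alpha and sidedness consistently with Section 12.1.
- State that the other markers and visits, qPCR and serology are supportive or exploratory, reported as estimates with 95% confidence intervals. This follows the additional-measures tier already in Section 9.1; align Section 8.2.1 with it.
- Describe day-60 biomarkers as values before atorvastatin or placebo, not as an efficacy comparison.

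This needs wording only: no new data, visits or patients. The downside is that fewer markers can carry an efficacy claim. A Holm procedure across the secondary markers is not needed and would cost power. For 0.40 against 0.20 with 75 per group, first-step power over ten markers falls from about 77% at two-sided 5% to about 45% at 0.5%.

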##### **7.1.3.1. Parasite-dependent immune-mediated myocardial damage:**

During primo-infection, shortly after macrophage invasion, IL-12/TNF- $\alpha$ -stimulated NK cells produce a peak of IFN- $\gamma$  secretion to control parasite replication at the expense of decreasing IL-10 production (Cardillo et al., 1996). IL-12 production further contributes to polarizing the immune response towards a wide diversity of pro- and anti-inflammatory profiles (Hasegawa et al., 2002), which explains, in part, the evasion of the immune response.

Due to the parasite's persistence, the host's fate is toward a low-grade but permanent state of immune system activation. In such a scenario, the T-cell response is essential for maintaining the typically low parasitemia in the chronic phase of the disease. However, CCC has a defective cytotoxic T cell response with the gradual depletion of the CD8+ T cell population (Perez-Anton et al., 2020). Furthermore, the TH1/TH2 balance is essential for progression to CCC. The parasite induces a combined response where the balance between excess proinflammatory (IFN- $\gamma$ , TNF- $\alpha$ , IL-1 $\beta$ ) and anti-inflammatory (IL-4, IL-10) cytokines may be critical in the development of CCC (Acevedo et al., 2018). Special mention deserves the TH17 subset as elevated levels of IL-17A may correlate with milder heart disease (Sousa et al., 2017).

*From the above, IFN- $\gamma$ , IL-1 $\beta$ , IL-4, IL-17A, and IL-10 levels could help predict CD progression and outcome after drug therapy (Llaguno et al., 2019), and the inclusion of anti-inflammatory drugs could favorably incline toward a better immune response profile and improve treatment of CCC.*

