### 9.7. Assessments:

On admission to the PCC, patients will undergo a complete medical history with an emphasis on CD, demographic data and medication history, physical examination, body weight and height, vital signs, and body temperature.

Ten ml of blood will be collected, in separate tubes, for hematological and biochemical evaluations: hemoglobin, total and differential white blood cell count, platelet count, CK, ALT, AST, GGT, alkaline

phosphatase, total and direct bilirubin, a lipid profile: total cholesterol, c-HDL, and c-LDL, triglycerides, fasting blood glucose and creatinine. A serum pregnancy test will also be performed. This test will be performed in the clinical laboratories of each center.

A 3 mL blood sample will be collected for conventional CD serology at each center's clinical laboratories and for a confirmatory serology test to be performed at the ISPCCH or an accredited laboratory.

5 mL of blood will be collected for qPCR. For clinical development and proof of concept, it has been proposed to use quantitative PCR parasitological tests as markers of efficacy in clinical studies of chronic indeterminate CD (Parrado et al., 2019). Thus, the real-time PCR technique described by Duffy et al. will be used in this assay (Duffy et al., 2013). Blood samples will be immediately added to a tube containing a volume (10mL) of a solution of guanidine/CIH 6M EDTA 0.2M 0.2M guanidine/CIH buffer 0.2M pH 8.0 (GEB) (Schijman et al., 2003). Samples with guanidine buffer can remain at room temperature for up to 30 days. For longer periods, it is necessary to store them in a refrigerator. After DNA extraction, samples will be processed using a commercial kit on an Applied 155 Biosystems 7300 RT-PCR system (Thermo Fisher).

An additional 3 ml of blood will be drawn for the biomarkers: BNP, cTnT, IFN- $\gamma$ , IL-1 $\beta$ , IL-4, IL-17A, and IL-10, sICAM-1, sVCAM-1, sE-selectin. These markers were selected following a literature review (Cortes-Serra et al., 2020; Echeverría et al., 2020; Llaguno et al., 2019). Serum levels of these markers will be determined using a multiplex approach with a Luminex 200 (R&Dsystems). To establish biological reproducibility, a pilot study will be performed before the sample analyses of this assay.

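### Goal 8.2.1 lists IL-4, IL-10 and IL-17A for decrease against the protocol's own rationale, 12.4 leaves its biomarkers unnamed, and TNF-alpha is a stated measure with no assay

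*Protocol*

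**What the plan says.** **The goal.** Section 8.2.1, repeated in the Summary (section 6), opens with "To evaluate the efficacy of the combination of ATO and antichagasic therapy to decrease". Its first bullet is "Inflammation, as measured by plasma levels of the cytokines", followed by TNF-alpha, IFN-gamma and then "IL-10, IL-1B, IL-4, and IL-17A". The list is not split by expected direction.

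**The rationale.** Section 7.1.3.1 sets IFN-gamma, TNF-alpha and IL-1beta, as pro-inflammatory, against a second group: the balance between the first group and the "anti-inflammatory (IL-4, IL-10) cytokines may be critical in the development of CCC". On the TH17 subset it adds that "elevated levels of IL-17A may correlate with milder heart disease".

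**The test.** Section 12.4, also in the Summary, plans for the primary outcome a Fisher's exact test, one-sided, on "the proportion of patients with a significant decrease in biomarker levels". It gives no list of markers, no number that must fall and no threshold. Secondary comparisons of proportions get an exact test with no sidedness stated.

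**The assays.** Section 9.7 states "An additional 3 ml of blood will be drawn for the biomarkers" and lists ten: BNP, cTnT, IFN-gamma, IL-1beta, IL-4, IL-17A, IL-10, sICAM-1, sVCAM-1 and sE-selectin. Footnote b of the schedule in 9.6 and footnote b of the Summary flowchart give the same ten. TNF-alpha is in none of the three.

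**The primary outcome.** Sections 9.1 and 12.1 name only two biomarkers, BNP and cTnT, both described as markers of cardiac function.

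**The concern.** A rule that scores decrease as benefit suits a marker only if lower is better for that marker. For IL-4 and IL-10 the protocol's argument points the other way: a drug that moves the balance towards an anti-inflammatory profile should not be credited for lowering its anti-inflammatory side. For IL-17A the only direction that the protocol gives is that higher may be better. If these three cytokines enter a one-sided responder definition, a fall could help a patient count as a responder, and a rise that the rationale would welcome could not be registered.

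The TNF-alpha point is simpler. A measure named in a goal but absent from every assay list cannot be reported, and no later analysis document can restore it. Section 9.7 describes no storage of biomarker serum for later assay.

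**Working it through.** No power or error-rate figure is involved. The check sets the passages side by side and counts.

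**Step 1: markers against sections.**

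| Marker | Under decrease in 8.2.1 | In the three assay lists | Direction given in 7.1.3.1 |
|---|---|---|---|
| TNF-alpha | yes | **no** | pro-inflammatory |
| IFN-gamma | yes | yes | pro-inflammatory |
| IL-1beta | yes | yes | pro-inflammatory |
| IL-4 | yes | yes | **anti-inflammatory** |
| IL-10 | yes | yes | **anti-inflammatory** |
| IL-17A | yes | yes | **higher may go with milder disease** |
| sE-selectin, sICAM-1, sVCAM-1 | yes | yes | none; 7.1.3.4 has them rise with endothelial activation |
| BNP, cTnT | yes | yes | none; no conflict with decrease |

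**Step 2: counts.**
- Cytokines named in 8.2.1: 6.
- Markers assayed: 5 cytokines + 3 adhesion molecules + 2 cardiac markers = 10.
- Named but not assayed: 6 − 5 = 1 (TNF-alpha).
- Assayed markers whose stated direction runs against the rationale: 3, which is 3/5 = 60% of the assayed cytokines and 3/10 = 30% of the panel.

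These are counts of markers. They do not measure an effect on the result.

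**Step 3: what 12.4 could mean.**
- *Ten-marker reading.* 12.4 uses the word biomarker without qualification. Wherever the protocol enumerates that word (9.7 and both footnotes b), it gives all ten markers. The next sentence of 12.4 also speaks of several different markers. On this reading IL-4, IL-10 and IL-17A are scored for a fall, and the one-sided test cannot credit a rise.
- *Two-marker reading.* 12.4 says that the test is for the primary outcome. The biomarkers in that outcome (9.1) and in the sample-size responder (12.1) are BNP and cTnT. On this reading the primary test has no direction problem.

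The text does not settle which is meant.

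**Step 4: what holds under both readings.** The conflict between 8.2.1 and 7.1.3.1 remains, because it does not depend on 12.4. So does the TNF-alpha gap. Section 9.1 also speaks neutrally of change in the inflammation and endothelial markers, so the protocol is directional in one place and neutral in another.

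**The case against.** A reader might infer that the plan scores a fall in every biomarker as benefit, that it regards these three cytokines as protective, and that harm would therefore be declared success. The documents do not support this.

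- 12.4 does not say every biomarker, and the two-marker reading agrees with 9.1 and 12.1.
- One-sidedness is stated only for the primary test. The cytokines belong to a secondary goal and to the additional measures in 9.1.
- 7.1.3.1 does not use the word protective. It calls IL-4 and IL-10 anti-inflammatory, says that the balance may be critical, and hedges the IL-17A statement. That a fall in any of them is harmful is an inference.
- The heading of 8.2.1 is loosely worded. The same verb also covers cardiac function and ejection fraction, which nobody intends to lower. The cytokine bullet can be read as lowering inflammation, with the panel as its measure.

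All of this stands, and it limits the point to what could happen under one reading of 12.4. It does not remove the point: even on the loose reading of 8.2.1 no direction is given for each marker, and the only one that 12.4 supplies is decrease.

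It may also be said that directions and thresholds for secondary markers can be left to a statistical analysis plan. That is fair for thresholds. Here, however, the protocol itself states a direction and fixes the assay list.

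On TNF-alpha, the sentence that closes 7.1.3.1 names only the five assayed cytokines, so a stray entry in 8.2.1 is plausible. That bears on which remedy to choose. It does not remove the mismatch.

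**Conclusion.** The point holds in limited form, as a minor to moderate correction.

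- **Certain from the text:** 8.2.1 lists IL-4, IL-10 and IL-17A for decrease, against the direction suggested in 7.1.3.1 (3 of 5 assayed cytokines). TNF-alpha is named in 8.2.1 and the Summary and is in none of the three assay lists (1 of 6 named cytokines with no data).
- **Conditional:** the primary test is affected only if 12.4 means the ten-marker panel. If it means BNP and cTnT, it is not.

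The direction conflict rests on taking the hedged statements in 7.1.3.1 as the protocol's own expectation. It does not rest on any outside claim about what these cytokines do.

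**What to change.** 1. **12.4 and the matching Summary text:** name the markers. Limit any biomarker decrease in the primary analysis to BNP and cTnT, consistent with 9.1 and 12.1. A wider responder built on falls in cytokines and adhesion molecules should not be written into 12.4, because it would conflict with those two sections.
2. **8.2.1 and the matching Summary text:** restrict decrease to the pro-inflammatory cytokines and the adhesion molecules. Analyse IL-4, IL-10 and IL-17A separately as two-sided changes. The cardiac bullet should have its own wording, since the present verb also covers ejection fraction.
3. **TNF-alpha:** either add it to the multiplex panel in 9.7 and to both footnotes b, using the same 3 mL sample, or delete it from 8.2.1 and the Summary.

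Items 1 and 2 cost wording only. Item 3 costs either a deletion or one more analyte on a planned assay, with no extra blood draw. With biomarker sampling on days 0, 60, 120 and 360, the added analyte means at most 300 × 4 = 1,200 determinations. The directions should be fixed before unblinding. TNF-alpha should be settled before the samples are assayed.
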